### Sample size

The primary outcome of concern was the rate of moderate or severe COPD exacerbations amongst the participants. The TORCH study of combined long-acting beta agonists and corticosteroids found yearly moderate or severe exacerbation rates dropped from 1.13 in the placebo group to 0.85 in the combination therapy group, giving a rate ratio of 0.75 [61]. The study was sized to duplicate a reduction of this size – using a negative binomial model for exacerbation rates as recent analyses have used these, rather than Poisson models, as the negative binomial models better account for individual patient variability [61,62]. A “k” parameter (the shape parameter of the associated gamma distribution) of 0.46 was used as a reanalysis of the TRISTAN data found this the most appropriate (95%CI 0.34-0.60) [62]. These parameters, with a confidence level of 95% and a power of 80% yield an estimated required group size per arm of 239, which allowing for a 15% drop out rate (greater than the 10% found in the *Housing, Insulation and Health study* for the over 65s due to the greater illness of this study population) suggested an initial sample size of 550 participants. If the “k” parameter was 0.4 then the required group size per arm would have been 230, if 0.6 then it would have been 262. If the baseline exacerbation rate was 1.0 rather than 1.13 then the required group size per arm would be 260. Therefore 550 participants was the target sample size.

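### The stated 239 per arm cannot be reproduced from the plan's inputs: on the usual two-sided, one-year reading it gives about 72% power, not 80%, and k is mislabelled as a gamma shape

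*Protocol article*

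**What the plan says.** All of the material is in the Sample size section of the protocol article. The planning effect comes from an earlier drug trial in which "yearly moderate or severe exacerbation rates dropped from 1.13 in the placebo group to 0.85 in the combination therapy group". The section rounds the resulting ratio to 0.75. The calculation was made "using a negative binomial model for exacerbation rates as recent analyses have used these, rather than Poisson models". The value of k is 0.46, described as "the shape parameter of the associated gamma distribution". The result is: "These parameters, with a confidence level of 95% and a power of 80% yield an estimated required group size per arm of 239".

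Three sensitivity sizes follow: 230 per arm for k = 0.4, 262 for k = 0.6, and for a lower control rate, "If the baseline exacerbation rate was 1.0 rather than 1.13 then the required group size per arm would be 260". The 239 is then raised for 15% dropout to reach a target of 550. The section does not say whether the test is one- or two-sided, gives no follow-up time beyond quoting yearly rates, and names no formula.

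**The concern.** The section presents 239 as following directly from its listed inputs. With yearly rates, a negative binomial variance and a 95% confidence level, most statisticians would use a two-sided 5% test over one person-year, and that calculation gives a clearly larger number. If that is the intended test, the chance of missing the planned effect at 239 per arm is about 28%, not 20%, and a null result would be read against a power claim that the inputs do not support.

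The label on k is a second, independent problem. In a gamma-Poisson mixture a larger shape means less overdispersion, so the required size should fall as the shape rises. The stated sizes do the opposite.

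**Working it through.** **Inputs from the Sample size section:** control rate 1.13, treated rate 0.85 (ratio 0.752, quoted as 0.75), k = 0.46, 95% confidence, 80% power.

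**Assumptions, because the section is silent:** two-sided 5%, exposure of one year, equal arms, and k as dispersion (variance = mu + k·mu²).

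**Formula (Wald test of the log rate ratio):** n per arm = (z_alpha + z_beta)² × (1/mu1 + 1/mu2 + 2k) / [ln(mu2/mu1)]²

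**Attempt to reproduce 239**
- (1.960 + 0.842)² = 7.849
- 1/1.13 + 1/0.85 + 2 × 0.46 = 0.885 + 1.176 + 0.920 = 2.981
- [ln(0.85/1.13)]² = (−0.2847)² = 0.08107
- n = 7.849 × 2.981 / 0.08107 = 288.6, so 289. At a ratio of exactly 0.75, n = 283.1, so 284.

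The stated 239 is not reproduced.

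**All four scenarios, two-sided, one year**

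| Control rate | k | Stated | Needed (ratio 0.752) | Needed / stated | Needed (ratio 0.75) | Power at stated size |
|---|---|---|---|---|---|---|
| 1.13 | 0.46 | 239 | 288.6 | 1.21 | 283.1 | 72.2% (73.0% at 0.75) |
| 1.13 | 0.40 | 230 | 277.0 | 1.20 | 271.7 | 72.3% (73.2%) |
| 1.13 | 0.60 | 262 | 315.7 | 1.21 | 309.6 | 72.3% (73.1%) |
| 1.00 | 0.46 | 260 | 314.6 | 1.21 | 308.5 | 72.1% (73.0%) |

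Power at 239 is Phi(0.2847 × √(239/2.981) − 1.960) = Phi(0.589) = 72.2%. In 4,000 simulated negative binomial trials with estimated dispersion, two-sided power was 71% at 239 per arm and 81% at 289.

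**Other two-sided forms.** Null variance from the control, pooled or treated rate gives 269, 286 or 308. A rate-difference test gives 290. None comes down to 239.

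**One-sided 5%.** The multiplier is (1.645 + 0.842)² = 6.183. Then n = 6.183 × 2.981 / 0.08107 = 227.4, so 228 (223 at ratio 0.75). Power at 239 is 81.7%, or 82.4% at ratio 0.75. The plain one-sided formula also misses 239, this time from below.

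**Direction of k.** The stated sizes are 230, 239 and 262 for k of 0.40, 0.46 and 0.60. They rise with k, as the 2k term requires if k is the dispersion. If k were the shape, the dispersion would be 1/k and the need would fall: 684, 620 and 522 per arm.

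**The case against.** The strongest counter-case is that the shortfall depends on conventions the section never states. The primary research question is directional (whether the subsidy reduces exacerbations), and under a one-sided 5% test 239 per arm has about 82% power. A less common one-sided form, with the null variance at the treated rate and a ratio of 0.75, gives 237, 228, 258 and 259, within about 1.4% of every stated size. A two-sided test with about 1.33 years of exposure gives 239, 228, 266 and 259, within 3%. The step from k = 0.4 to 0.6 also leans one-sided: the section adds 32 per arm, against about 30 one-sided and 38 to 39 two-sided at any exposure.

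Much of this stands. A reader might infer from the near-constant factor of 1.2 that a wrong multiplier was used throughout. The document does not support that, because an undisclosed convention would leave the same pattern. Equally, nothing in the text points to a one-sided test, to that variance form, or to exposure beyond a year. A 95% confidence level ordinarily means two-sided 5%, and the Data analysis section speaks only of differences between groups.

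Two further inferences should be resisted. One is that the trial really needed about 620 per arm: that follows only from taking the shape label literally, and the section's own sensitivity sizes rule it out. The other is that the mislabelled k will distort the simulated residual envelope in the Data analysis section: nothing there says the planning value of 0.46 is used for it.

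**Conclusion.** The point holds in a conditional form. Given two-sided 5% testing, one year per person and k as dispersion, the stated inputs need about 289 per arm (284 at ratio 0.75), and 239 provides about 72 to 73% power; the other three sizes fall short by the same factor. With one year per person, 239 passes 80% only if the test is one-sided, which is not disclosed. Why the figures differ cannot be determined from the document, and it would go too far to state 72% as the trial's power without naming the convention.

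The k label is wrong whatever the sidedness or exposure, because the stated sizes rise with k.

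Confidence is high in the two-sided, one-year arithmetic and in the label, and low on the cause. The stated power is a figure that readers will rely on, but the analysis model, endpoint and effect estimate are unaffected.

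**What to change.** In the Sample size section:

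1. State the sidedness of the test, the exposure time per person and the formula behind 239.
2. If testing is two-sided over one year, restate power at 239 per arm as about 72% and replace 239, 230, 262 and 260 with 289, 277, 316 and 315 (or 284, 272, 310 and 309 if the ratio is fixed at 0.75).
3. If a one-sided test or another exposure was intended, say so and restate all four sizes and the power on that basis.
4. Relabel k as the negative binomial dispersion parameter, the reciprocal of the gamma shape.

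This costs wording only. No extra enrolment is asked for; the one drawback is a less favourable stated power if the two-sided reading is confirmed.

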**Methods:**

Participants had a clinician diagnosis of COPD and had either been hospitalised or taken steroids or antibiotics for COPD in the previous three years; their median age was 71 years. Participants were recruited from three communities between 2009 to early 2011. Where possible, participants’ houses were retrofitted with insulation. After baseline data were received, participants were randomised to either ‘early’ or ‘late’ intervention groups. The intervention was a voucher of $500 directly credited to the participants’ electricity company account. Early group participants received the voucher the first winter they were enrolled in the study, late participants during the second winter. Objective measures included spirometry and indoor temperatures and subjective measures included questions about participant health and wellbeing, heating, medication and visits to health professionals. Objective health care usage data included hospitalisation and primary care visits. Assessments of electricity use were obtained through electricity companies using unique customer numbers.

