**Discussion:**

This community trial has successfully enrolled 522 older people with COPD. Baseline data showed that, despite having a chronic respiratory illness, participants are frequently cold in their houses and economise on heating.

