### Participants

The demographic characteristics of the 522 COPD participants enrolled are presented in Table 1; 20% were Māori, 77% New Zealand European or European and 2% Pacific peoples, and 3% reported belonging to other ethnic groupings, with only 3% of people reporting more than one ethnicity. We used the ethnicity classifications recommended by Statistics New Zealand. We succeeded in recruiting an older population (median age 71), with nearly a fifth (18%) of participants being over 80 at baseline.

**Table 1 T1:** Baseline characteristics of participants

**Characteristic**	**% (number)**
General health fair or poor	47% (216/460)
Phlegm most days a week	52% (239/458)
Shortness of breath most days a week	62% (288/461)
4 or more bouts of severe chest trouble over winter	22% (99/457)
Able to walk only 100m or less on the flat before stopping for breath	42% (192/457)
At least one cold/flu over winter	65% (294/453)
Ever told have heart disease	47% (210/446)
Ever told have at least 2 of heart disease, cancer, liver disease, renal disease, diabetes, arthritis	42% (179/430)
On home oxygen	8% (39/460)
Received flu vaccine	84% (387/458)
Received pneumonia (pneumococcal) vaccine	22% (96/420)
Lived in dwelling for more than 9 years	63% (290/463)
Dwelling built before 1977	72% (303/422)
Own the dwelling	76% (350/462)
Dwelling always cold	42% (196/462)
Cold at least partly to keep cost of heating down	48% (213/445)
Shivered inside at least once previous winter	56% (249/445)
‘Dragon breath’ inside at least once previous winter	39% (177/450)
Plug in medical equipment	21% (94/454)
Gave “no other choice” as a reason for main form of heating	43% (193/450)
Gave cheap or easy to budget with as reason for main form of heating	29% (129/450)
Eligible for a high use health card*	60% (251/416)
Eligible for community services card **	77% (337/438)
Receive a disability allowance	51% (220/435)
Currently smoke daily	17% (81/463)
European ethnicity	77% (349/452)
Māori ethnicity	20% (92/452)
Pacific ethnicity	2% (10/452)
Male	50% (228/456)
Aged under 65	27% (122/455)
Aged over 80	18% (81/455)
Median age	71 Years

*This card entitles some frequent users of health services to reduced health co-payments.

** This card entitles people on low income to reduced health (and some other) co-payments.

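### The 15% drop-out allowance was multiplied on instead of divided out, and at that planned loss the 522 enrolled leave about 222 per arm, short of the required 239

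*Protocol article*

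**What the plan says.** The Sample size section of the protocol article starts from TORCH rates that "dropped from 1.13 in the placebo group to 0.85 in the combination therapy group, giving a rate ratio of 0.75". It takes a negative binomial k "of 0.46 was used as a reanalysis of the TRISTAN data found this the most appropriate", and states that these inputs, "with a confidence level of 95% and a power of 80% yield an estimated required group size per arm of 239". It then allows for 15% drop-out, above the 10% seen in an earlier housing study, which is "due to the greater illness of this study population) suggested an initial sample size of 550 participants". The section ends by confirming 550 as the target.

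On the number achieved, the Abstract says: "This community trial has successfully enrolled 522 older people with COPD". The Participants section says: "The demographic characteristics of the 522 COPD participants enrolled are presented in Table 1". The denominators in Table 1 run from 416 to 463.

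On sequence, the Abstract says: "After baseline data were received, participants were randomised". The section on wave design and randomisation counts a person as recruited once both consent and baseline data are in, and puts the baseline interview before randomisation.

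**The concern.** A drop-out rate is a share of those enrolled, so the required number of completers has to be divided by one minus that rate. Adding 15% of the completers gives a smaller figure that does not leave 239 per arm after a 15% loss. Enrolment then fell short of that figure as well. The article gives both the target and the achieved number and calls enrolment successful, but it does not say what the achieved number does to the stated 80% power.

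The Table 1 denominators raise a related question. If baseline data came before randomisation, and the table describes all 522, rows that each lack 59 or more people need an explanation. The answer bears on how many were randomised. It also bears on adjusted models, because the Data analysis section lists baseline severity, smoking and immunisation as possible covariates.

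**Working it through.** **Inputs.** From the Sample size section: 239 per arm (478 in total), 80% power, 95% confidence (taken as a two-sided 5% test), rates 1.13 and 0.85 per year, k = 0.46, drop-out 15%, earlier drop-out 10%, target 550. From the Abstract and the Participants section: 522 enrolled. Equal allocation is assumed from the single group size per arm.

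**1. Reproducing the target.** 478 x 1.15 = 549.7, which rounds to 550. The stated target is therefore the multiplied version.

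**2. Dividing out the loss.** 478/(1 - 0.15) = 562.4, so 563. Per arm, 239/0.85 = 281.2, so 282, or 564 in total. The difference from 550 is 13 to 14 people, about 2.5%.

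**3. What each total leaves per arm.**

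| Enrolled | Loss | Left per arm | Against 239 |
|---|---|---|---|
| 550 | 15% | 550 x 0.85/2 = 233.8 | about 5 short |
| 522 | 15% | 522 x 0.85/2 = 221.9 | about 17 short |
| 522 | 10% | 522 x 0.90/2 = 234.9 | about 4 short |

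The largest tolerable loss is 1 - 478/550 = 13.1% for 550 and 1 - 478/522 = 8.4% for 522.

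**4. Power, taking 239 per arm as 80%.** Power(n) = Φ[(1.96 + 0.8416) x √(n/239) - 1.96].

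- n = 233.8 (550, 15% loss): Φ(0.811) = about 79%.
- n = 221.9 (522, 15% loss): Φ(0.739) = about 77%.

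**5. Power directly from the stated rates.** The section quotes "yearly moderate or severe exacerbation rates" but gives no exposure time in the calculation, so one year per participant is an assumption. k is treated as the dispersion, because the article's own required size rises with k. The variance term is V = 1/1.13 + 1/0.85 + 2 x 0.46 = 2.981, and ln(0.85/1.13) = -0.285.

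- n = 239: SE = √(2.981/239) = 0.1117; 0.285/0.1117 = 2.55; power = Φ(2.55 - 1.96) = about 72%.
- n = 233.8: about 71%.
- n = 221.9: about 69%.

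On this scale, 80% would need (1.96 + 0.8416)² x 2.981/0.285² = about 289 per arm. The step from 80% to 72% is there before any drop-out or enrolment shortfall. Those two add about 1 point (72% to 71%) and a further 2 points (71% to 69%).

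**6. Table 1.** The largest denominator is 463 (years in the dwelling; daily smoking) and the smallest is 416 (high use health card). So 522 - 463 = 59 people (11%) are missing from even the fullest row, and 522 - 416 = 106 (20%) from the emptiest. Sex has 456 and age 455.

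**The case against.** The inflation slip is slight. It is well inside the article's own sensitivity range of 230 to 262 per arm, and recruitment has closed, so a corrected target changes nothing in the field. That stands for the slip taken alone. It does not cover the enrolment shortfall, since 222 per arm is below even the most favourable figure, 230.

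A reader might infer that 239 per arm cannot be met. The documents do not support that: 522 exceeds 478, and 239 is met at 8.4% loss or less. Hospitalisations come from national records and primary care data from providers (Other data), so missing a questionnaire need not mean losing the outcome. The supportable statement is that 239 is not met at the planned 15% loss or at the earlier 10%.

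A reader might also infer that only 463 people have baseline data, or that 59 were randomised without any. Neither follows. 463 is the maximum for one item. Someone missing that item may have answered others, and height, weight and spirometry were also collected (Data collection) but are not in Table 1. At least 463 people have some baseline data, so at most 59 have none. The Recruitment section confirms acceptance once consent is returned, before baseline, so 522 may count an earlier stage than randomisation. The participant flow figure, not available here, may settle this.

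Finally, a reader might set 69% against the planned 80% and blame enrolment. Step 5 shows that most of that gap lies in the 239 itself.

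**Conclusion.** The point holds in a limited form. The target should have been 563 to 564, not 550, an error worth about 1 point of power. At 522 enrolled and the planned 15% loss, about 222 per arm remain. If 239 gives 80%, as the article states, power is then about 77%. This rests on equal allocation, a two-sided 5% test and loss at the plan's own rate.

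That 239 gives only about 72% by the standard negative binomial formula with one year of exposure is a larger and separate matter. It should not be attributed to drop-out or enrolment.

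The mismatch between 522 and the Table 1 denominators is a request for reconciliation, not a demonstrated breach of procedure. The 463 is neither the number randomised nor a cap on the number analysable.

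**What to change.** - In the Sample size section, replace 550 with 563 (564 for equal arms), or state that 550 allows for 13.1% loss.
- Restate power for the 522 enrolled at the planned loss: about 77% if 239 is accepted as 80%. If the figure is recomputed from the rates instead, give 72% for 239 beside 69% for 222, so that the cause of the gap is clear.
- State the number randomised per arm, and say which stage 522 refers to.
- Under Table 1, explain why every row lacks at least 59 of the 522.
- Confirm that everyone randomised stays in the primary analysis whether or not baseline items are missing, unless the full protocol or analysis plan already says so.

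The cost is wording and a slightly less favourable power figure. No further patients need to be enrolled.

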### Recruitment

From 2009 until December 2010, application forms were distributed through various agencies, including primary health organisations, COPD support groups, public hospital outpatient departments, and community health workers. Letters of invitation were also sent to eligible people discharged after a hospitalisation for COPD. Concerted attempts were made to follow up incomplete application forms, so that literacy difficulties did not automatically disqualify applicants. On receipt of an eligible application form, potential participants were sent an information sheet, personal consent forms for the person with COPD and another adult in the household (optional) and a reply-paid envelope. If the property was rented, consent forms were included for the landlord to agree to retrofitter assessment and insulation.

When the signed consent form was returned, the applicant was sent a letter confirming their acceptance into the study. Where necessary and feasible, ceiling and under-floor insulation were upgraded or retrofitted in homes.

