### Temperature of New Zealand homes

Compared to other countries with similar climates, houses in New Zealand are colder, with an *average* winter evening living room temperature of 17.9°C and a mean range of 10°C- 23.8°C [34]. Often only one room, usually the living room, is heated during winter [35]. Average winter overnight bedroom temperatures fall below 14°C [36], indicating that many bedrooms are colder than this for all or part of winter.

The World Health Organization included the elderly in groups vulnerable to low indoor temperatures in the home, and stated that below 16°C there was a serious risk to health, and between 16°C and 19°C there were small risks to health after substantial periods of time [37]. In England and Wales if people are home all day acceptable temperatures are defined as 21°C in the main living area and 18°C in other occupied rooms [38], but the New Zealand Building Code’s only relevant specification is that the interior temperature of old people’s homes and early childhood centres should be able to be maintained at a minimum of 16°C [39].

There are suggestions that higher morbidity, as well as mortality, may be compounded by energy-inefficient or poorly heated housing, particularly for older people [40-43]. Research we have previously conducted found that insulating houses led to a significantly warmer, drier indoor environment and resulted in improved health and a trend for fewer hospital admissions for respiratory conditions [44,45]. The addition of more effective, sustainable heating, as well as retrofitted insulation, in houses where there were children with asthma problems, reduced asthma symptoms, visits to the doctor and school absences [46].

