### Wave design and randomisation

As winter was the crucial period for the study, and recruitment is often slow at the start of the process the study was deliberately designed to recruit over two years in ‘waves’. Participants were recruited from three communities from 2009 to early 2011. Those recruited (i.e. consent and baseline data received) by June (early winter in the southern hemisphere) 2010 were assigned to Wave 1, those recruited later were assigned to Wave 2. Each wave was randomised into early and late intervention groups – the early group receiving the intervention the first winter in which the wave was enrolled in the study, and the late group the following winter. Thus *Wave 1- Early* participants received the fuel subsidy during 2010; *Wave 1- Late* and *Wave 2- Early* participants received the subsidy during 2011; *Wave 2- Late* participants received the subsidy during the winter of 2012. The randomisation was carried out by a statistician external to the study team.

The configuration of an autumn baseline with a spring follow-up was chosen in recognition of the significant illness of the sickest participants; with a full winter baseline there could have been more of a bias towards only the least unwell people completing the study. We allowed for a greater drop-out rate than we usually experience due to the illness among the study population.

As the intervention was carried out at a dwelling level, in order to avoid clustering, we selected only one primary participant per household, the person best able to complete the study questionnaire. The baseline interviews were carried out before randomisation so that knowledge of their group allocation could not affect the participants’ measures. In order to utilise the voucher for additional heating, the participants were then informed of their group allocation. Although the interviewers also knew the participant’s group allocation, they were trained to avoid mentioning group allocation status during interactions with the participants to minimise any recall bias. The analyses will be carried out with the researchers blinded to the meaning of the intervention group code. We also included several indicators designed to measure each participant’s propensity to report positive change and will control for the placebo effect by conducting sensitivity analyses using these propensity to positivity scores.

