#### Outcome measures

**Acceptability of methods** The overall feedback from the majority of the participants in the WHEZ Study has, to date, been very positive. One such indicative report from a Wellington interviewer described her assessment of participants’ experiences in more detail:

“Although at the initial visit some participants had concerns and were unsure about the study, once they were given more information and further explanation of the study then they willingly and happily participated. In the first year pre-winter visits most of the participants reported how cold and damp their homes were and with the escalating cost of electricity they had to minimize how often they could have the heaters on to warm their homes. In the post–winter visit, the first wave of participants that received the subsidy of $500 commented how grateful and thankful they were for the subsidy because it helped tremendously - especially with the high winter electricity power bills. They also reported on the change in warmth in their homes since they had been insulated.”

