### Data analysis

Generalised linear models will be fitted to the data. Covariates potentially included in the model will be study arm, current medication, age, sex, region, baseline severity, smoking status and immunisation status (influenza and pneumococcal). The appropriateness of a Poisson or negative binomial model of exacerbations will be confirmed by examining the residuals of the observed data fitted to the postulated models against an envelope of residuals from a set of simulated trials. If the observed residuals fall inside the simulated envelope then the model is considered to fit adequately. A non-parametric test – rank analysis of covariance – will be used to confirm differences between the groups.

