#### Cost-benefit analysis

The design of a cost-benefit analysis of this study is straightforward and follows similar studies’ methods [70,71]. The cost side of the intervention follows from providing a $500 voucher for electricity (and knowing the amount of electricity actually used). On the benefit side, the principal quantifiable outcome is reduced hospitalisations (ideally, exacerbation-reduced or exacerbation-free years would be measurable, but this was beyond the scope of the study). In addition, the study will estimate and value changes in pharmaceutical usage.

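### The study insulated homes as well as paying vouchers, but no dwelling variable is among the candidate covariates and the voucher and cost-benefit claims are not limited to that setting

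*Protocol article*

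**What the plan says.** All references are to the protocol article.

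- **Insulation.** Recruitment states: "Where necessary and feasible, ceiling and under-floor insulation were upgraded or retrofitted in homes". The abstract also mentions insulation without naming an arm, in this order: "houses were retrofitted with insulation. After baseline data were received, participants were randomised". For rented homes, Recruitment adds that the landlord was asked to agree to an assessment by the retrofitter and to the work.
- **What insulation does.** Under Temperature of New Zealand homes, the authors report from their own earlier research that "insulating houses led to a significantly warmer, drier indoor environment and resulted in improved health". The Discussion adds that it cuts fuel bills and raises indoor temperature.
- **What is randomised.** "Each wave was randomised into early and late intervention groups" (Wave design and randomisation). The groups differ in which winter the voucher is paid.
- **Analysis model.** "Covariates potentially included in the model will be study arm, current medication, age, sex, region, baseline severity, smoking status and immunisation status" (Data analysis). Immunisation closes the list.
- **Outcomes.** Table 2 lists room temperature and electricity usage as secondary outcomes. Data collection describes temperature loggers placed in winter and collected in spring.
- **Claims.** Research questions and Conclusions refer to the electricity subsidy or voucher only. Intervention presents the sum as feasible for a national policy. On costs: "The cost side of the intervention follows from providing a $500 voucher for electricity" (Cost-benefit analysis).

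**The concern.** The study delivered two things that act on the same pathway, and only one of them was randomised. The other appears neither in the named covariates nor in the limits placed on the conclusion.

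Two things are at stake.

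- **Precision.** Whether a home is insulated should be one of the stronger predictors of its winter temperature and electricity use. As described, the loggers run only in winter, so no pre-winter temperature reading is available to stand in for the thermal quality of the dwelling.
- **Transfer.** The pooled voucher effect is an average over whatever mix of insulated and uninsulated homes the study ended up with. A voucher paid nationally, without a retrofit offer, would meet a different mix. A reader of the question, the cost-benefit section or the conclusion is not told this.

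**Working it through.** **1. Is there a figure in the plan to reproduce?** No. The article gives no number of homes insulated, no completion dates and no effect of insulation on any trial outcome. The nearest figures are in Table 1: 72% (303/422) of dwellings built before 1977, and 76% (350/462) owned, so 24% not owned. Neither is insulation status.

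**2. Does omitting insulation bias the contrast?** Let T be the voucher arm and I the insulation status, with log rate = a + bT + cI. If I is unrelated to T, averaging over I gives a mean of exp(a + bT) × E[exp(cI)] in each arm. The last factor is the same in both arms and cancels, leaving the rate ratio exp(b). For temperature or electricity use on a linear scale, the cI term cancels in the difference in the same way. The article never links insulation to arm, so on what is written there is no bias.

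**3. What does omission cost?** If insulation class explains a share R² of the outcome variance left after the other covariates, adjusting for it multiplies the standard error by about √(1 − R²). The documents do not fix R², so I put no number on it. R² should be larger for temperature and electricity use, on which insulation acts directly, than for exacerbations.

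**4. Is costing only the voucher wrong?** Per household, in the winter when only the early group is paid:

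- early group: insulation cost + $500 + health-care cost (early)
- late group: insulation cost + health-care cost (late)
- difference: $500 + health-care cost (early) − health-care cost (late)

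The expected insulation cost is equal in the two arms and drops out. The voucher is therefore the correct incremental cost for the contrast that was randomised.

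**5. What does the pooled effect describe?** If a share p of homes is insulated, the pooled log rate ratio is approximately p × (log ratio in insulated homes) + (1 − p) × (log ratio in other homes). It carries over to a population with a different p only if the two log ratios are equal. The article reports no p and gives no ground for equality. The direction of any difference is also open: an insulated home holds bought heat better but needs less of it.

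**6. Could the trial estimate the difference between classes?** Not well. Let V be the variance of the overall voucher effect. With two classes in shares p and 1 − p, the difference between class effects has variance V/p + V/(1 − p) = V/[p(1 − p)]. Assume p between 50% and 80%, since the documents give no value:

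| p | p(1 − p) | Variance | Standard error relative to overall effect |
|---|---|---|---|
| 0.50 | 0.25 | 4V | 2.0 |
| 0.80 | 0.16 | 6.25V | 2.5 |

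Enrolment was 522 against a target of 550 that was set for the overall effect alone, so any estimate by class can only be exploratory.

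**The case against.** The strongest reply is that this is a caveat on generalisability and no more. The covariates are described as possible, so the list is open and an analysis plan could add to it. A condensed article need not give retrofit dates. The Discussion openly says that the study acts on both thermal quality and fuel cost. The Conclusions section restates the aim and reports no effect.

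Much of that stands. Disclosure in the Discussion, however, does not limit the research question, the cost-benefit section or the stated conclusion. The list, although open, names eight candidates, and none describes the dwelling while two of the outcomes do.

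A reader might infer more than the document supports:

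- **That the comparison is confounded by insulation.** Nothing links insulation to arm (step 2).
- **That insulation coincided with the first voucher winter.** The only support is one interviewer's undated report about first-wave voucher recipients: "They also reported on the change in warmth in their homes since they had been insulated". The abstract mentions retrofitting before randomisation, and neither place gives dates.
- **That retrofit cost is wrongly left out.** It cancels in the randomised contrast (step 4).
- **That first-versus-second-winter comparisons mix the two treatments.** No such within-person analysis is stated; the treatment term is study arm.
- **That the trial measures a voucher on top of insulation.** Homes that needed no work, or could not have it, were not excluded, so the effect is an average over mixed status.
- **That the voucher works better, or worse, in insulated homes by some stated amount.** The documents support neither a size nor a direction.

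**Conclusion.** The point holds as one of precision and interpretation. The randomised early-versus-late contrast is valid as described, and its costing is right. What is lost is some precision, chiefly for temperature and electricity use, and a stated limit on the policy inference: the effect and net benefit belong to a voucher given where insulation was also offered if feasible, not to a voucher alone.

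Neither loss can be sized from the article. The conclusion rests on two assumptions: that insulation was unrelated to arm, which the text implies but does not show with data; and that insulation predicts temperature and electricity use, which the authors themselves assert. A table by arm would test the first.

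**What to change.** 1. **Covariate.** Classify each dwelling at randomisation as already adequate, retrofitted before randomisation, or not retrofitted (including pending), using the retrofitter assessment. Prespecify this class in the models, above all for temperature and electricity use. Use status at randomisation rather than later status, because participants knew their allocation and later completion could depend on it.
2. **Reporting.** Tabulate insulation status and completion date by arm. This would show any imbalance and settle the timing question.
3. **Effect by class.** Report a voucher-by-class estimate, labelled exploratory.
4. **Wording.** State in the conclusion and the cost-benefit section that the effect and net benefit apply to a voucher given where insulation was offered if feasible.

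The cost is one baseline covariate, one table, one exploratory estimate and a sentence in each of two sections. The analysis is still written in the future tense, so the change is possible. It assumes that the retrofit assessments and dates can be recovered; the article mentions an assessment but does not say what was kept. The downside is that class-specific estimates will be imprecise and the policy claim narrower.
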